#### Overview

2.6.1

Testing is completed over 2 days at baseline and post-intervention. Order of days is divided by a collection of biospecimens (i.e., blood and muscle tissue) and non-physical tests (i.e., questionnaires and body composition) completed on 1 day, and all other physically demanding tests are completed on the other (∼2–3 days apart). This separation of measures is to ensure participants can recover from the biopsy and not complete any physically demanding activities that may influence blood or muscle biomarkers. All measures are collected at all time points by study staff members trained in exercise oncology unless otherwise specified (Table 1).

**Table 1 T1:** Outcome measures by study visits for the FIERCE trial.

Timepoint	Week 0	Week 1–17	Week 18	Week 19–34^a^
Enrollment				
Eligibility screen	X			
Phone screen	X			
Informed consent	X			
Randomization	X			
Interventions				
Circuit training + self-directed aerobic exercise		X		X (optional)
Attention control		X		
Assessments				
Fried frailty phenotype measures	X		X	
Muscle biopsy (optional)	X		X	
Blood biomarkers	X		X	
Anthropometrics	X		X	
Patient-reported outcomes	X		X	
Cardiorespiratory fitness	X		X	
Physical function	X		X	
Strength	X		X	
Physical activity	X	X	X	
Diet	X		X	
Exit survey			X	

^a^
Applies to the attention control group and is optional.

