##### Muscle biopsy

2.6.3.2

Skeletal muscle biopsies of the vastus lateralis are optional, where participants are asked at the time of consent if they wish to partake. Skeletal muscle-derived biomarkers to be assessed include myokines [IL-6, IL-15, secreted protein acidic and rich in cysteine (SPARC), oncostatin M (OSM), decorin, irisin] and insulin pathway-related biomarkers (GLUT-4 receptors, IGF-1, IGFBP-3). The muscle biopsy is performed by a qualified nurse practitioner and/or physician assistant.

The local area (quadriceps thigh muscle) is anesthetized with a numbing spray, followed by an injection of lidocaine. A cannula (∼13.5-gauge) is then inserted into the vastus lateralis muscle perpendicularly, such that it pierces through the layer of fascia surrounding the muscle fibers. To obtain the biopsy, the needle is fed through the cannula, and the biopsy trigger is activated, resulting in a spring-loaded, rapid collection of ∼10–15 mg muscle tissue. The cannula remains inserted into the muscle, the needle is removed, and the procedure is repeated until an adequate sample is collected. After sampling is complete, the cannula is removed, and pressure is applied to the area to stop any potential bleeding, with a bandage placed over the biopsy site to promote healthy healing. The muscle sample is briefly washed on clean gauze and frozen using liquid nitrogen for storage at −80°C for later batched analysis. The biopsies occur following a 12 h fast. The post-intervention biopsy is performed at a distance of ∼1 cm from the first incision and 72–96 h after the last training session for participants in the exercise to reflect resting levels of mRNA expression (43).

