### Sample size calculation

2.11

We will enrol a total of 80 eligible participants. Considering a 10% attrition rate, the sample size of the analysis population will be 72. We plan to accrue participants for 24 months. The Wilcoxon rank-sum test will be used to compare the score based on the frailty phenotype (37) between the two groups for the primary analysis. Table 4 shows the anticipated distribution of the score in each group (59). With a sample size of 72, the study will have 84% to detect the relative effect of 0.30 at a 0.05 two-sided alpha level. This power calculation was performed by the WMWssp package (60). For comparing each of the five criteria of the frailty score (binary outcomes), the sample size of 72 will provide 80% power to detect a moderate effect size (Cohen's *h* = 0.415) at a 0.05 two-sided alpha level (61). For each continuous outcome, two-sample *t*-tests will be used for the between-group comparison as the primary analysis. Log transformation may be considered, if appropriate. With a sample size of 72, the study will have 80% power to detect a moderate to large effect size (Cohen's *d* = 0.67) at a 0.05 two-sided alpha level.

**Table 4 T4:** Sample size and power with the anticipated distribution of the frailty score (0–5).

Frailty status	Not frail (%)	Pre-frail (%)		Frail (%)			Total sample size	Relative effect	Power (%)
	0	1	2	3	4	5			
Attention control	15	63	17	4	1	0	72	0.30	84
Intervention	85	14	1	0	0	0			

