### Statistical analysis

2.12

This study will assess whether a 16-week, multicomponent exercise intervention will improve the frailty status of mPCa on ADT. Furthermore, we will assess the effect of the intervention on sarcopenia status, skeletal muscle-derived biomarkers, and cell proliferation rate.

A total of 80 eligible patients who complete the baseline assessment will be randomly assigned to the exercise or attention control groups in an allocation ratio of 1:1 using a permuted blocked design with varying block size (with investigators blinded to block size). The randomization will be stratified by frailty status (pre-frail vs. frail) at baseline assessment.

All analyses will be performed based on the intention-to-treat principle. We will repeat the same analyses with the subjects who complied with the protocol as secondary analyses. Baseline demographic and clinical measures, as well as baseline values of trial outcomes, will be presented by randomized intervention group; continuous measures will be summarized by mean (SD) or median (IQR) and categorical measures by frequencies (percent's). The randomized groups will be compared concerning baseline demographic and clinical variables using two-sample *t*-tests, Wilcoxon rank-sum tests, or Fisher's exact tests to confirm baseline comparability. These variables will be included in the adjusted analyses if clinically meaningful or statistically significant differences are identified.

The primary outcome is the score based on the Fried frailty phenotype (37), which consists of five criteria, and the score will take an integer value from 0 to 5. The Wilcoxon rank-sum test will be used as the primary analysis for comparing the score distribution between groups. Mean score and a corresponding 0.95 confidence interval (CI) will be calculated. We will also assess the intervention effect on each of the five criteria for the frailty phenotype for hypothesis generation purposes. For each, we will perform Fisher's exact test for the between-group comparison and estimate an odds ratio and a corresponding 0.95 CI. Regression analysis will be used to identify baseline factors associated with the outcomes, where proportional odds models will be used for the score as an ordered categorical variable with six categories, and logistic regression models will be used for each of the five criteria.

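### The 80% power stated for every continuous outcome assumes 72 participants, which the optional biopsy does not secure for the muscle markers

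*Protocol article*

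**What the plan says.** Section 2.11 of the protocol article sets the numbers: "We will enrol a total of 80 eligible participants", and then "Considering a 10% attrition rate, the sample size of the analysis population will be 72". Attrition is the only loss allowed for. The section then turns to the continuous outcomes, beginning "For each continuous outcome, two-sample" (t-tests), and gives them a single power statement: "With a sample size of 72, the study will have 80% power to detect a moderate to large effect size", with Cohen's d equal to "0.67) at a 0.05 two-sided alpha level".

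Section 2.6.3.2 describes how the muscle markers are obtained: "Skeletal muscle biopsies of the vastus lateralis are optional, where participants are asked at the time of consent if they wish to partake". Table 1 also marks the biopsy as optional at week 0 and week 18, and section 2.8 repeats this when describing compensation. The markers are six myokines (IL-6, IL-15, SPARC, OSM, decorin, irisin) and three insulin-pathway markers (GLUT-4, IGF-1, IGFBP-3). The Introduction and section 2.6.3 make them secondary outcomes, the fourth hypothesis in the Introduction concerns them, and section 2.12 lists them among the intervention effects to be assessed. The article gives no expected biopsy uptake, and no separate power figure or exception for these outcomes.

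**The concern.** A power figure tied to 72 participants applies to an outcome only if about 72 participants supply it. Attrition alone already brings 80 down to 72. For the muscle markers there is a second source of loss, refusal of the biopsy, and the calculation makes no allowance for it. Read literally, the reference to each continuous outcome credits these markers with 80% power at d = 0.67, which the design does not secure.

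What is at stake is interpretation. Someone relying on section 2.11 could take a non-significant muscle-marker result as fair evidence against an effect of d = 0.67, when the chance of detecting such an effect may have been well below 80%. Section 3 presents the biopsies as a strength, and its limitations do not mention that they are optional.

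**Working it through.** **Inputs.** From section 2.11: 80 enrolled, 10% attrition, two-sample t-test, d = 0.67, two-sided alpha 0.05, stated power 80%. From section 2.12: participants are "randomly assigned to the exercise or attention control groups in an allocation ratio of 1:1". Biopsy uptake is not in the article, so it is varied below as an assumption.

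**Step 1: analysis population.** 80 × 0.90 = 72, or 36 per arm. This reproduces.

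**Step 2: the plan's own power figure.** For n per arm, the t-test has 2n − 2 degrees of freedom and noncentrality d × √(n/2). With n = 36, the degrees of freedom are 70 and the noncentrality is 0.67 × √18 = 2.84. The noncentral t distribution then gives 80.05% power, and the d detectable with 80% power is 0.670. The stated figure is therefore correct for 36 per arm.

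**Step 3: reserve.** Solving for n at d = 0.67 and 80% power gives 35.96 per arm, so 36 leaves no slack. With 70 participants in total, power is 78.9%. With 68 (four completers without a biopsy), it is 77.7%.

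**Step 4: uptake needed.** With the article's own 10% attrition, all 72 completers must have biopsy data. Even with no attrition at all, 72/80 = 90% of those enrolled would have to accept.

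**Step 5: range of uptake.** Uptake is taken as a share of the 72 and split evenly between arms, using the formula in step 2. For example, 50% uptake gives n = 18, 34 degrees of freedom and noncentrality 0.67 × √9 = 2.01.

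| Assumed share of the 72 with biopsy data | n per arm | Power at d = 0.67 | Detectable d at 80% power |
|---|---|---|---|
| 100% | 36 | 80.1% | 0.67 |
| 90% | 32.4 | 75.7% | 0.71 |
| 80% | 28.8 | 70.5% | 0.75 |
| 75% | 27 | 67.6% | 0.78 |
| 50% | 18 | 49.7% | 0.96 |
| 25% | 9 | 26.7% | 1.41 |

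The direction is the same throughout: with fewer than 72, power is below the stated 80%. How far below depends entirely on uptake.

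**The case against.** The strongest reply is that nothing was miscalculated. The sentence is conditional on 72 participants, is true on that condition, and names no muscle marker. That stands: the fault is in the scope of the statement, and the arithmetic is sound. It does not remove the point, because the same section applies the statement to every continuous outcome and the article never exempts the biopsy markers.

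A second reply is that an article condenses a fuller protocol, where biopsy targets may be given. This also stands as far as it goes: a missing uptake figure is not the complaint. The complaint is that what the article does state is too broad.

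Third, low uptake cannot be presumed, since section 2.8 provides payment for each biopsy. A reader might infer that the muscle analyses could detect only very large effects. The article does not support that: at 90% or 80% uptake the detectable d is 0.71 or 0.75, not far above 0.67.

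Fourth, a reader might infer that only participants with usable tissue at both visits count. The Introduction speaks of change for the secondary outcomes, which makes pairing plausible. But section 2.12 specifies a between-group t-test without saying it is on change scores, adds mixed models, and uses whatever data are available under a missing-at-random assumption. Complete pairs are not clearly required, and the point does not depend on them, since even a single week-18 biopsy is optional.

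Finally, secondary outcomes need not be powered, and section 2.12 already plans confidence intervals for the continuous outcomes. Both are fair. However, those intervals are described for each group, whereas the one that matters here is for the difference between groups.

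**Conclusion.** The point holds as a matter of scope. The 80% power at d = 0.67 is right for 36 per arm but has no reserve, and it is stated for all continuous outcomes although the muscle markers depend on consent to an optional procedure. For those markers it fails unless essentially every completer provides biopsy data.

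The direction is certain; the size is not. Under the assumed range of 90% down to 50% of the 72, power at d = 0.67 runs from 76% to 50%, and the detectable d from 0.71 to 0.96. These figures assume an even split between arms.

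The primary frailty analysis is unaffected. So are the blood biomarkers and DXA measures, which are not described as optional and for which 72 can stand.

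**What to change.** In section 2.11, limit the n = 72, d = 0.67, 80% statement to continuous outcomes measured in all participants. Add one line for the biopsy outcomes with the expected number of participants with biopsy data and the d detectable at 80% power for that number; for example, 18 per arm corresponds to d = 0.96. The expected number should come from the sponsor's own uptake estimate, since the article gives none. The same restriction would also take out the CT-based skeletal muscle index, which section 2.6.2.1.1 makes available only in a subset.

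State that a null muscle-marker result will be interpreted by the confidence interval for the between-group difference, and not by the 80% figure. Relabelling these outcomes as hypothesis-generating is a choice open to the investigators, but the correction does not require it.

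The cost is a few sentences and a less favourable figure for the muscle markers. Enrolment and trial conduct do not change.

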### Statistical analysis

2.12

This study will assess whether a 16-week, multicomponent exercise intervention will improve the frailty status of mPCa on ADT. Furthermore, we will assess the effect of the intervention on sarcopenia status, skeletal muscle-derived biomarkers, and cell proliferation rate.

A total of 80 eligible patients who complete the baseline assessment will be randomly assigned to the exercise or attention control groups in an allocation ratio of 1:1 using a permuted blocked design with varying block size (with investigators blinded to block size). The randomization will be stratified by frailty status (pre-frail vs. frail) at baseline assessment.

All analyses will be performed based on the intention-to-treat principle. We will repeat the same analyses with the subjects who complied with the protocol as secondary analyses. Baseline demographic and clinical measures, as well as baseline values of trial outcomes, will be presented by randomized intervention group; continuous measures will be summarized by mean (SD) or median (IQR) and categorical measures by frequencies (percent's). The randomized groups will be compared concerning baseline demographic and clinical variables using two-sample *t*-tests, Wilcoxon rank-sum tests, or Fisher's exact tests to confirm baseline comparability. These variables will be included in the adjusted analyses if clinically meaningful or statistically significant differences are identified.

The primary outcome is the score based on the Fried frailty phenotype (37), which consists of five criteria, and the score will take an integer value from 0 to 5. The Wilcoxon rank-sum test will be used as the primary analysis for comparing the score distribution between groups. Mean score and a corresponding 0.95 confidence interval (CI) will be calculated. We will also assess the intervention effect on each of the five criteria for the frailty phenotype for hypothesis generation purposes. For each, we will perform Fisher's exact test for the between-group comparison and estimate an odds ratio and a corresponding 0.95 CI. Regression analysis will be used to identify baseline factors associated with the outcomes, where proportional odds models will be used for the score as an ordered categorical variable with six categories, and logistic regression models will be used for each of the five criteria.

For other outcome continuous variables, mean, median, and corresponding 0.95 CIs will be calculated in each group. The primary comparison will be performed by two-sample *t*-tests. To assess the robustness of findings, Wilcoxon rank-sum tests will also be performed as secondary analyses. ANOVA models will also be used to identify baseline factors associated with the outcomes. Log transformation may be considered, if appropriate.

For longitudinal data, we will use generalized linear mixed-effect models with an appropriate link function (i.e., identity-link for continuous outcomes and logit-link for binary outcomes). The independent variables will include an indicator variable for the randomized intervention, time, and intervention-by-time interaction. Random intercepts (and random slopes) will be specified at the subject level. The within-subject correlation structure will be determined prior to evaluation of the between-group difference, using information criterion measures to determine the correlation structure providing the best model fit. In the model, the main effect of the intervention will test for group differences over the entire study period. Regarding missing values, the primary analysis will be all available data analysis, assuming that the missing mechanism is missing at random. As sensitivity analyses, we will apply multiple imputations (62).

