#### Control group

2.7.2

During this initial 16-week period, control participants are provided a booklet with the prescribed stretching program to be completed 7 days per week to match the prescribed frequency of exercise sessions in the exercise group, e.g., 3 days/week supervised circuit training plus 4 days/week self-directed aerobic exercise. The stretching program is self-directed home-based with instruction provided at baseline testing only to orient them with the booklet. Similar to the exercise program, the stretches change every 4 weeks, where 4–5 stretches that target both upper and lower body are prescribed. Participants in the attention control group are offered the supervised component of the 16-week intervention following the initial 16-week period.

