### Intervention adherence

2.8

Exercise adherence is captured for the multicomponent exercise intervention by calculating (1) the percentage of supervised circuit trainings attended (out of 48 sessions) and self-directed exercise sessions completed (out of 64 sessions) and (2) relative dose intensities of supervised circuit trainings. Reasons for missed sessions will be documented throughout the study. However, to account for any unforeseen illness, family or medical emergency, or unplanned travel, all participants may have a total of 18 weeks to complete the 48 supervised exercise sessions. Participants are considered compliant if they attend ≥70% of the total prescribed number of supervised exercise sessions (e.g., attend ≥34 out of 48 sessions), ≥70% of the self-directed exercise sessions (e.g., complete ≥45 out of 64 sessions), and complete ≥70% of the supervised resistance sessions at the prescribed intensity. Participants are provided with monetary compensation for each optional muscle biopsy and testing visit and parking validation for every visit to Dana-Farber Cancer Institute.

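### The secondary complier analysis can draw only on a compliance rule for the exercise arm, so it is likely to favour exercise

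*Protocol article*

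**What the plan says.** Section 2.12 (Statistical analysis) sets the main principle: "All analyses will be performed based on the intention-to-treat principle". It then adds: "We will repeat the same analyses with the subjects who complied with the protocol as secondary analyses". It does not define the complying subjects there.

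The one definition of compliance is in section 2.8 (Intervention adherence), which opens with "Exercise adherence is captured for the multicomponent exercise intervention by calculating". The rule follows: "Participants are considered compliant if they attend ≥70% of the total prescribed number of supervised exercise sessions", given as at least 34 of 48. The man must also complete at least 70% of the self-directed exercise sessions (45 of 64) and "complete ≥70% of the supervised resistance sessions at the prescribed intensity".

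Section 2.7.2 (Control group) prescribes stretching on 7 days a week from a booklet. On delivery it says: "The stretching program is self-directed home-based with instruction provided at baseline testing only". Section 2.6.5.7 (Physical activity) gives controls weekly activity logs, but no stated rule turns these logs into a compliance status.

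**The concern.** Repeating the same analyses means repeating the between-group tests in a restricted set. That set is to be chosen by compliance, and the only rule available describes sessions that controls are never prescribed. Either no control qualifies and there is no comparison, or controls enter without an equivalent filter.

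Under the second reading, men who could not sustain a demanding programme leave one arm only. The article itself suggests that this selection is related to prognosis:

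- Section 2.7.1 has the day's resistance exercise adjusted when bone pain is reported, while the third criterion counts sessions at the prescribed intensity.
- Section 2.8 names illness and medical emergency among the reasons for allowing extra weeks to complete the sessions.
- Exhaustion, slowness and weakness are components of the primary score.

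The complier result will be read beside the primary one. In an analysis set of 72 it could show a benefit where the intention-to-treat result does not.

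**Working it through.** **The plan's own cut-offs.** Supervised sessions: 3 × 16 = 48, and 0.70 × 48 = 33.6, rounded up to 34. Self-directed sessions: 4 × 16 = 64, and 0.70 × 64 = 44.8, rounded up to 45. Both stated figures reproduce, and both denominators are exercise-arm sessions. The control prescription would be 7 × 16 = 112 stretching sessions, for which no cut-off is given.

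**Inputs for the bias.**

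- From section 2.11: 80 × 0.9 = 72 analysed, so 36 per arm at 1:1.
- Assumed, because the article gives neither figure: the share of exercisers meeting all three criteria, p = 0.6 to 0.8, and the correlation between adherence and a better week-18 outcome, r = 0 to 0.5.
- Simplification: a normally distributed outcome with SD 1 and a two-sided 5% t-test, standing in for the 0–5 score and its Wilcoxon test.

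**Formula.** With no true effect, if exercisers are kept only when in the top share p of adherence and all 36 controls are kept, the expected spurious difference is r × φ(z)/p, where z is the normal quantile at 1 − p. The factor φ(z)/p is:

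- p = 0.6: 0.386/0.6 = 0.644
- p = 0.7: 0.348/0.7 = 0.497
- p = 0.8: 0.280/0.8 = 0.350

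**Results.** Each cell gives the bias in SD and, after it, the false-rejection rate from 20,000 simulated trials.

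| r | p = 0.6 | p = 0.7 | p = 0.8 |
|---|---|---|---|
| 0 | 0; 4.8% | 0; 4.7% | 0; 4.8% |
| 0.1 | 0.06; 5.2% | 0.05; 5.6% | 0.04; 5.2% |
| 0.2 | 0.13; 7.5% | 0.10; 6.3% | 0.07; 6.0% |
| 0.3 | 0.19; 10.5% | 0.15; 8.7% | 0.10; 7.0% |
| 0.5 | 0.32; 21.8% | 0.25; 15.8% | 0.17; 10.7% |

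If identical selection (same p, same r) could be applied in both arms, the simulated false-rejection rate would be 4.7–5.3%.

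**With a true complier effect of 0.50 SD and none in non-compliers.** At r = 0.3–0.5 the unadjusted contrast returns about 0.50 + 0.10 = 0.60 to 0.50 + 0.32 = 0.82 SD. The randomisation-based estimate (intention-to-treat difference divided by p) averaged 0.48–0.50 SD in simulation, and −0.02 to 0.00 SD under no effect.

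**Precision at p = 0.7.** Unadjusted contrast, 25 compliers against 36 controls: √(1/25 + 1/36) = 0.26 SD. Randomisation-based estimate: √(2/36)/0.7 = 0.236/0.7 = 0.34 SD.

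**If non-compliers also benefit.** Suppose they gain half of the 0.50 SD effect (an assumption). The randomisation-based estimate becomes [0.50p + 0.25(1 − p)]/p, which is 0.67, 0.61 and 0.56 SD at p = 0.6, 0.7 and 0.8. It then overstates the complier effect by 0.06–0.17 SD.

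**The case against.** A reader might infer that the plan says every control enters the complier set. It does not. Section 2.12 does not cite section 2.8, controls do have a stretching programme to comply with, their activity is logged, and section 2.10 says that data are monitored for adherence to the protocol. The full protocol may define compliance for controls, and an article need not reproduce that definition. What remains is that the article does state a numerical rule and a between-group analysis, and the two do not fit together.

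A stretching threshold for controls would make the analysis workable. It would restore comparability only if it selected the same kind of men, and completing a home booklet is unlikely to select as 34 supervised visits plus 45 aerobic sessions do.

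The size of the bias rests on assumed values. At a correlation of 0.2 or less, false rejection stays between about 5% and 7.5%.

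The strongest objection is to the remedy. Under section 2.8 a man who attends all 48 supervised sessions but completes 44 of 64 home sessions is non-compliant, yet he may well benefit. Dividing by the compliant share then credits his gain to the compliers. That objection stands, and the fix has to address it. A ratio of mean differences also does not reproduce the planned Wilcoxon, Fisher or proportional-odds analyses.

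**Conclusion.** The point holds in a limited form. The planned complier analysis has one compliance rule to rely on, and that rule applies to the exercise arm only. The comparison that can actually be run is therefore likely to favour exercise: by 0.10–0.32 SD, with about 7–22% false rejection, if 60–80% comply and adherence correlates 0.3–0.5 with outcome.

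It would go too far to say that the analysis is biased as a matter of fact. The documents give neither the compliance rate nor the correlation, and at zero correlation there is no bias. Nor is the trial's main conclusion at risk, since intention to treat governs it and the complier analysis is secondary. The change should still be made, because a supplementary estimate that keeps the randomised comparison needs only data the trial already collects.

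**What to change.** In section 2.12:

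- Label any complier-only comparison descriptive and report it without p-values.
- As the supplementary inferential estimate, report a complier average causal effect for the mean frailty score, with randomisation as the instrument and compliance as in section 2.8. In its simplest form this is the intention-to-treat difference in mean score divided by the proportion compliant in the exercise arm, with a bootstrap confidence interval. Controls are offered the supervised programme only after the first 16 weeks, so treating non-compliance as one-sided is a reasonable approximation.
- State the exclusion restriction, and that the estimate overstates the complier effect if exercise below the section 2.8 thresholds also helps.
- For that reason, add a sensitivity range for partial benefit. If non-compliers gain a fraction k of the complier effect, the divisor becomes p + (1 − p)k. At p = 0.7 and k = 0.5 this is 0.85, which recovers 0.50 SD from an intention-to-treat difference of 0.425 SD. Alternatively, use randomisation as the instrument for the number of sessions attended.

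The cost is a few lines of text and code and no new data. The downsides are a wider interval (standard error about 0.34 against 0.26 SD at 70% compliance) and an assumption that must be stated.

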##### Participant characteristics, health behaviors, and medical history

2.6.5.1

Participant demographic and medical history data were collected at baseline from medical records, and participants completed questionnaires. Information collected includes age, gender, race, ethnicity, non-cancer medical history, cancer history, family cancer history, anthropometric history, smoking habits, alcohol intake, medication use, and vitamin and supplement use.

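### Covariates for the supplementary adjusted analyses are chosen after the fact, by baseline significance tests or an undefined clinical judgement, and not fixed in advance by prognostic value

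*Protocol article*

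**What the plan says.** Section 2.12 of the protocol article sets out three steps for baseline data.

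- **Display.** Demographic and clinical measures, "as well as baseline values of trial outcomes, will be presented by randomized intervention group".
- **Testing.** "The randomized groups will be compared concerning baseline demographic and clinical variables". The methods named are the t-test and "Wilcoxon rank-sum tests, or Fisher's exact tests to confirm baseline comparability".
- **Selection.** "These variables will be included in the adjusted analyses if clinically meaningful or statistically significant differences are identified".

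Either trigger, clinical meaning or statistical significance, is enough to bring a variable in. No threshold is given for the first. Baseline outcome values are displayed by arm but are not named among the variables tested and carried forward. Neither the baseline Fried score nor the FRAIL stratum used in the randomisation (2.5, 2.12) is named as a covariate in any model.

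The main comparisons are fixed separately. For the Fried score, "The Wilcoxon rank-sum test will be used as the primary analysis for comparing the score distribution between groups". For continuous outcomes, the primary comparison is a two-sample t-test.

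**The concern.** Allocation is random, so any baseline difference between the arms is due to chance. A p-value for that difference answers a question whose answer is already known. Non-significance in a trial of this size is also weak evidence of balance.

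As a way of choosing covariates, the test looks at the wrong quantity. Adjustment helps when a variable predicts the outcome. A significance test measures only how far the arms happen to differ on it. The rule can therefore bring in a variable that is irrelevant to frailty and pass over a strong predictor with a moderate imbalance.

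The clinical-meaning trigger could pick up some of what the tests miss. But it has no threshold and is applied once the baseline data have been compared by arm, so the covariate set still depends on the data. What is at stake is the precision and credibility of the adjusted analyses.

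**Working it through.** **Inputs from the protocol article.** 80 randomised 1:1 (2.5, 2.11); analysis population 72 after 10% attrition, hence 36 per arm; d = 0.67 at 80% power and two-sided alpha 0.05 for continuous outcomes (2.11). Section 2.6.5.1 lists 12 baseline domains, among them gender, which cannot differ in an all-male trial.

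**Assumptions.** The article does not state the number of baseline tests; I take 5 to 20, independent. It gives no covariate-outcome correlation; I take rho = 0.3, 0.5 and 0.7.

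**1. The plan's own figure.** Two-sample t-test, 36 per arm, d = 0.67: power by the noncentral t distribution is 80.05%. The stated 80% is reproduced.

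**2. Chance of at least one false trigger.** With k independent tests at 0.05 this is 1 − 0.95^k.

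| k | Probability |
|---|---|
| 5 | 0.23 |
| 12 | 0.46 |
| 20 | 0.64 |

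**3. Smallest significant baseline difference.** This is t(0.975; 2n − 2) × √(2/n) in SD units. For n = 36: 1.994 × 0.2357 = 0.47 SD. For n = 40 it is 0.45 SD.

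**4. How often a sizeable imbalance is not significant.** A difference of 0.3 SD at 36 per arm is z = 0.3/0.2357 = 1.27, exceeded in either direction with probability about 0.20. Taking off the 0.05 that are significant leaves about 0.15. Simulation gives the same: about 15% of trials for a given covariate.

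**5. Consequence in those trials.** With no treatment effect, an unadjusted t-test then rejects in 6.5%, 8.4% and 10.9% of trials for rho = 0.3, 0.5 and 0.7. This is the conditional bias that adjustment would remove.

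**6. Performance over all trials.** Simulation with 36 per arm, one normal covariate and a normal outcome (40,000 runs for type I error, 20,000 for power). The selective rule adjusts only if the baseline test gives p < 0.05. The alternative is ANCOVA on the covariate in every trial.

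| rho | Type I error, selective | Type I error, always | Power at d = 0.67, selective | Power at d = 0.67, always |
|---|---|---|---|---|
| 0.3 | 4.8% | 5.0% | 80.2% | 83.0% |
| 0.5 | 4.1% | 4.9% | 80.5% | 89.4% |
| 0.7 | 3.6% | 5.0% | 81.5% | 97.3% |

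The selective rule gains almost nothing over no adjustment, which gives about 80% throughout. It does not inflate type I error. The simulation models the significance trigger alone, because the clinical-meaning trigger has no definition to simulate.

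**The case against.** The strongest reply is that the rule touches nothing that decides the trial. The primary Wilcoxon test and the t-tests are fixed and unadjusted. That stands. A reader might infer from step 5 that the primary result carries an inflated error rate because of this rule. The documents do not support that: those tests would be unadjusted whatever the rule said, the step 5 figures condition on imbalance in a minority of trials and on assumed correlations, and over all trials there is no inflation.

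Second, the rule has two triggers. It would be too strong to say that it leaves all non-significant prognostic imbalance unadjusted, since a difference judged clinically meaningful would enter. This also stands. The remaining criticism is that this trigger is undefined and applied after the data are compared. Section 2.5 says that study staff cannot be blinded to allocation, but the article does not say who makes the judgement or whether that person has seen outcomes, so nothing should be alleged on that score.

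Third, a reader might take the rule to be the plan's only protection against chance imbalance. It is not. Randomisation is stratified by frailty status, and in the mixed models for longitudinal data the intervention-by-time term would take account of baseline outcome values. The regression models for baseline factors also examine prognostic strength, though the article does not link them to covariate choice.

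Fourth, exact covariates are commonly left to a statistical analysis plan. But the article states a selection rule here. An analysis plan that fixed covariates in advance would contradict that rule.

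**Conclusion.** The point holds for the supplementary adjusted analyses and no further. Their covariates are to be picked from observed baseline differences, by tests that cannot do what is asked of them or by a judgement without a criterion. The plan names neither the baseline outcome value nor the randomisation stratum as a covariate.

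The chance of a false trigger is 23% to 64%, depending on the assumed number of independent tests. The precision lost against pre-specified adjustment is about 3, 9 and 16 percentage points of power at rho = 0.3, 0.5 and 0.7 (83.0 − 80.2, 89.4 − 80.5, 97.3 − 81.5). These losses rest on assumed correlations, a single normal covariate, a normal outcome and the significance trigger alone. They illustrate the continuous outcomes and do not transfer directly to the 0 to 5 Fried score. The change is worth making because it costs nothing, not because the primary conclusion is at risk.

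**What to change.** In section 2.12, delete the baseline significance tests and the sentence that selects covariates from them. Report the baseline table descriptively by arm.

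State that every adjusted model includes the baseline value of the outcome and the FRAIL randomisation stratum, whatever the observed balance. For the primary outcome, the baseline value is the baseline Fried score. Any further prognostic covariates are the sponsor's choice, but the list should be short and fixed before outcome data are analysed.

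The cost is wording only. Both variables are already collected: the Fried measures at baseline (Table 1) and FRAIL status at phone screening (2.3). The sample size, visits and primary test do not change. Section 2.3 describes recruitment as ongoing, so the article leaves room to make the change before outcomes are analysed.
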